## Abstract

**Background:**

The purpose of the PROLUCA study is to investigate the efficacy of preoperative and early postoperative rehabilitation in a non-hospital setting in patients with operable lung cancer with special focus on exercise.

**Methods:**

Using a 2x2 factorial design with continuous effect endpoint (Maximal Oxygen Uptake (VO_2_peak)), 380 patients with non-small cell lung cancer (NSCLC) stage I-IIIa referred for surgical resection will be randomly assigned to one of four groups: (1) preoperative and early postoperative rehabilitation (starting two weeks after surgery); (2) preoperative and late postoperative rehabilitation (starting six weeks after surgery); (3) early postoperative rehabilitation alone; (4) today’s standard care which is postoperative rehabilitation initiated six weeks after surgery. The preoperative rehabilitation program consists of an individually designed, 30-minute home-based exercise program performed daily. The postoperative rehabilitation program consists of a supervised group exercise program comprising cardiovascular and resistance training two-hour weekly for 12 weeks combined with individual counseling. The primary study endpoint is VO_2_peak and secondary endpoints include: Six-minute walk distance (6MWD), one-repetition-maximum (1RM), pulmonary function, patient-reported outcomes (PROs) on health-related quality of life (HRQoL), symptoms and side effects of the cancer disease and the treatment of the disease, anxiety, depression, wellbeing, lifestyle, hospitalization time, sick leave, work status, postoperative complications (up to 30 days after surgery) and survival. Endpoints will be assessed at baseline, the day before surgery, pre-intervention, post-intervention, six months after surgery and one year after surgery.

**Discussion:**

The results of the PROLUCA study may potentially contribute to the identification of the optimal perioperative rehabilitation for operable lung cancer patients focusing on exercise initiated immediately after diagnosis and rehabilitation shortly after surgery.

**Trial Registration:**

NCT01893580

## Background

Lung cancer is one of the most frequently occurring cancer diagnoses with the highest mortality rate [1]. Lung cancer is divided into Small-Cell Lung Carcinoma (SCLC) and Non-Small Cell Lung Carcinoma (NSCLC). Surgery is at present the primary treatment for NSCLC. According to the Danish Register of Lung Cancer 2011, the 2-year survival was 62% and the 5-year survival 42% following radical surgery for lung cancer [2]. Modern surgical treatment includes both minimal invasive surgery, e.g. video-assisted thoracoscopic surgery (VATS), and open surgery such as thoracotomy. An increasing proportion of lung cancer patients are operated by VATS technique in both Europe and the US. At Copenhagen University Hospital (Rigshospitalet), more than 60% of all lung cancers patients are operated by VATS [2].

Improved surgical techniques combined with effective adjuvant chemotherapy have led to a significant survival benefit in individuals with NSCLC [3,4]. Postoperative complications are experienced by 25% of the patients with NSCLC [2], and the risk of developing postoperative complications during the first two weeks after surgery has been reported to be dependent on different factors, e.g. preoperative cardiorespiratory capacity, measured as VO_2_peak [1,5]. The physiological consequences of ageing and inactivity combined with the cancer disease and the treatment of cancer result in a marked reduction in VO_2_peak and functional capacity [6-8]. Other factors such as smoking [9], alcohol consumption [10], nutritional status [11] and comorbidity [12] are predictors of postoperative complications. The treatment of NSCLC and other types of cancer is complex and potentially lethal. Accordingly, side effects are now recognized as a subject of major clinical importance [13]. The side effects may comprise physical and psychological as well as social distress with symptoms such as reduced cardiorespiratory capacity, paresthesia, post-thoracotomy pain syndrome, fatigue, anxiety, and depression [14-16]. The late side effects are long-lasting or even chronic and may result in restrictions in activity of daily living and reduced quality of life [5,17-23].

A Cochrane systematic review from 2012 indicates that exercise in patients with a variety of cancer diagnoses may have beneficial effects on HRQoL [24]. This is supported by a Danish randomized controlled trial with 269 cancer patients (different diagnoses) according to which patients receiving chemotherapy tolerate intensive physical exercise and experience reduced fatigue, depression, and nausea [25]. In general, rehabilitation in cancer patients based on physical exercise perioperatively has been shown to increase HRQoL and physical activity, and at the same time reduce the side effects of the treatment [24,26-33]. There is consistent evidence from 27 observational studies that physical activity is associated with reduced all-cause, breast cancer-specific, and colon cancer-specific mortality [34].

Clinical studies of *preoperative* physical exercise in patients with operable NSCLC are sparse. However, a recent prospective feasibility study on 25 patients with NSCLC reports that the patients tolerate 30 minutes of preoperative intensive cardiovascular exercise 5 times/week. The study finds that exercise significantly improves VO_2_peak and 6MWD [35]. Two other studies indicate that rehabilitation including preoperative exercise can improve physical and psychological outcome in patients with NSCLC [36,37].

The effect of *postoperative* physical exercise in patients with lung cancer has been investigated briefly. The studies differ in type of intervention, dose and timing of intervention, and the research is primarily based on case studies and studies with few and heterogeneous participants [36]. Two non-randomized feasibility studies observed that supervised moderate to high intensity cardiovascular exercise initiated four weeks after surgery is safe and feasible for operable lung cancer patients. The intervention consisted of three weekly cycling sessions for a period of 14 weeks, and participation was associated with a significantly improved HRQoL [38,39].

In a prospective study of 45 lung cancer patients, exercise on ergometer bikes 30 minutes daily, initiated two weeks after end of cancer treatment (including both surgery and chemotherapy), was reported to result in a pronounced improvement in exercise capacity and functional status [40]. The results are confirmed by other studies [41,42]. Another randomized study of 53 lobectomized lung cancer patients showed retention of muscle strength in the intervention group in which the patients participated in mobilization and strength exercise twice daily during admission followed by a 12-week long home exercise program. HRQoL (EORTC questionnaire) and physical capacity (measured by 6MWD) were unchanged [43]. Overall, these studies indicated that postoperative exercise may have a positive effect on physical capacity and HRQoL in NSCLC. A systematic review from 2011 concluded that pre- and postoperative exercise is safe and feasible for NSCLC patients and associated with a positive effect on physical capacity and, to some extent, HRQoL [26]. However, the main part of the studies quoted in the review are small case series and the only randomized study in the review observes no difference between the intervention and the control group [26]. In summary, several studies indicate that postoperative exercise of NSCLC patients is safe and associated with improvement of fitness and self-reported outcome such as HRQoL and fatigue [27,44]. Positive effects of perioperative exercise interventions are more pronounced with moderate- to vigorous-intensity versus mild-intensity exercise programs. More research is required to fully understand the potential effect of exercise over time and to determine essential attributes of exercise (mode, intensity, frequency, duration, and timing) by cancer type and cancer treatment [24].

To our knowledge the present Perioperative Rehabilitation in Operation for LUng CAncer (PROLUCA) study is the first study to investigate the clinical effects of pre- and early postoperative rehabilitation in NSCLC patients. In PROLUCA a randomized clinical trial, the efficacy of pre- and early postoperative rehabilitation is compared with the effect of rehabilitation initiated six weeks after surgery (usual care) in a non-hospital setting.

The aim of PROLUCA is to identify the optimal timing of exercise to improve VO_2_peak in postoperative NSCLC patients. The specific aims are: (1) comparison of combined preoperative home-based exercise with postoperative exercise regarding VO_2_peak and patient-reported outcomes (PROs), (2) comparison of early postoperative exercise (initiated as early as two weeks after surgery) with usual care regarding VO_2_peak and PROs.

## Methods

### Participants and settings

The study will recruit and randomize 380 patients (95 patients/study arm) with histologically or cytologically confirmed NSCLC, stage I-IIIa (TNM classification v. 7 [45]) or strong substantiated suspicion of NSCLC, referred for surgery. All subjects are assigned for curative lung cancer surgery at Department of Cardiothoracic Surgery, Copenhagen University Hospital (Rigshospitalet). The inclusion and exclusion criteria are described in Table 1: Subject Eligibility Criteria in the PROLUCA Trial.

**Table 1 T1:** Subject eligibility criteria in the PROLUCA trial

**Inclusion criteria**	
All subjects are assigned for curative lung cancer surgery at Department of Cardiothoracic Surgery RT at Copenhagen University Hospital (Rigshospitalet).	Screened for eligibility criteria at Bispebjerg University Hospital and Gentofte Hospital.
At least 18 years old.	
Performance status 0–2 (WHO) [46].	Capable of participating in the described tests and intervention.
Living in the City of Copenhagen or surrounding Municipalities.	Reside within driving distance of Copenhagen Centre for Cancer and Health and capable of managing transportation as necessitated by the clinic-based assessments and supervised exercise interventions.
Ability to read and understand Danish.	
Approval by primary surgeon.	To examine for any contraindication in participating in physical exercise.
**Exclusion criteria**	
Presence of metastatic disease or surgical inoperability.	
Diagnosis of Lung Cancer not verified by histological diagnosis.	
Cardiac disease [6,47].	Decompensated heart failure, severe aortic stenosis, uncontrolled arrhythmia, acute coronary syndrome.
Contraindications to maximal exercise testing as recommended by the American Thoracic Society and exercise testing guidelines for cancer patients [48].	

### Procedure

The study is conducted in accordance with the CONSORT (Consolidated Standards of Reporting Trials) statement for non-pharmacologic interventions and the Helsinki Declaration [49]. Informed consent is obtained from all participants prior to initiation of any study procedures. The study is approved by The Danish National Committee on Health Research Ethics (H-3-2012-028) and the Danish Data Protection Agency (2007-58-0015).

The study flow is presented in Figure 1 Study Flow PROLUCA. Using a 4-arm, randomized design, potential subjects will be identified and screened for eligibility and informed about PROLUCA by the study research coordinators at the involved hospitals (Bispebjerg University Hospital and Gentofte Hospital). After referral to intended curative lung cancer surgery at Copenhagen University Hospital (Rigshospitalet), the subjects are contacted by telephone and provided with a review of the study. If the subjects accept to participate, the baseline assessment is performed at Copenhagen Centre for Cancer and Health. At baseline the following assessments are performed: (1) PROs described in Table 2 Data Assessment Schedule in the PROLUCA Trial, (2) anthropometric data, (3) 6MWD, (4) muscle strength (1RM in chest- and leg-press machines), (5) pulmonary function test, and (6) cardiopulmonary exercise test (VO_2_peak). All baseline assessments will be completed as close to time of diagnosis as possible and repeated the day before surgery, pre-intervention (6MWD, pulmonary function, FACT-L), post-intervention, and at follow-up six months and one year after surgery.

**Figure 1 F1:**
[figure not shown]
Study Flow PROLUCA.

**Table 2 T2:** Data assessment schedule in the PROLUCA trial

	**Baseline**^ **a** ^	**Flw-up**^ **b** ^	**Flw-up**^ **c** ^	**Flw-up**^ **d** ^	**Flw-up**^ **e** ^	**Flw-up**^ **f** ^
Anthropometric data and cancer disease	X	X		X	X	X
	**Physiological measurements**					
Cardiorespiratory capacity (VO_2_peak)	X	X		X	X	X
Six- minute walk distance (6MWD)	X	X	X	X	X	X
One-repetition-maximum (1RM)	X	X		X	X	X
Heart rate (HR), Blood pressure (BP)	X	X		X	X	X
Spirometric (FEV_1_/FEV_1_%)	X	X		X	X	X
	**Patient-reported outcome**					
Health-related quality of life (EORTC QLQ-C30, FACT-L)	X	X	FACT-L	X	X	X
Symptoms and side effects (EORTC–LC13)	X	X		X	X	X
Anxiety and depression (HADS)	X	X		X	X	X
Well-being (SF-36)	X	X		X	X	X
Distress thermometer	X	X		X	X	X
Lifestyle	X	X		X	X	X
Sickness absence and work status	X	X		X	X	X
Social support (MSPSS)	X	X		X	X	X
	**Other measurements**					
Perioperative complications	X (30 days)	X (30 days)				
Duration of hospitalization	X (30 days)	X (30 days)				
Survival Histological diagnosis and TNM staging						X

^a^Baseline (0 week).

^b^Flw-up (Follow-up): Preoperation (the day before surgery).

^c^Flw-up (Follow-up): Pre-intervention (2/6 weeks after surgery).

^d^Flw-up (Follow-up): Post-intervention (14/18 weeks after surgery).

^e^Flw-up (Follow-up): Six months after surgery.

^f^Flw-up (Follow-up): One year after surgery.

### Group allocation (Randomization)

Following the successful completion of baseline assessments, participants will be randomly allocated, on an individual basis, to one of the four exercise intervention groups:

Group 1: Preoperative home-based exercise and postoperative rehabilitation initiated as early as two weeks after surgery.

Group 2: Preoperative home-based exercise and postoperative rehabilitation initiated six weeks after surgery.

Group 3: Postoperative rehabilitation initiated as early as two weeks after surgery.

Group 4: Postoperative rehabilitation initiated six weeks after surgery (Usual practice as control group).The random allocation sequences will be concealed from all study personnel and performed by Copenhagen Trial Unit, Centre for Clinical Intervention Research. A permuted block design with allocation weight of 1:1:1:1 will be used to generate the treatment assignments. Randomly allocated participants will remain in the same group for the entire duration of the intervention, as expressed in Figure 2 PROLUCA Study Timeline. To ensure similarity of randomized groups at baseline, patient randomization will be stratified based on type of surgery, VATS versus thoracotomy surgery.

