### Statistical considerations

#### ***Sample size calculation***

This randomized phase II trial will accrue 380 subjects with operable NSCLC over an accrual period of ~2 years. The present design consists of four intervention groups of equal size, and it is assumed that no interaction occurs between the groups. With the smallest clinical relevant difference set at 2 mLO_2_^.^ kg^-1 .^ min^-1^,95 participants are required in each group (power: 80%), giving a total inclusion of 380 patients.

For each of the primary and secondary endpoints, three separate t-tests will be used to compare each experimental arm to the control arm in mean change across time of the endpoint. For each endpoint, the overall alpha level will be controlled at a two-sided 0.05 by using Holm's procedure [65]. That is, Holm's procedure first ranks the three p-values from lowest to highest. The first (lowest) p-value has to be less than 0.05/3 (0.0167) to be significant and permit continuation to the other t-tests. The Holm's procedure continues sequentially in this fashion using alpha levels of 0.05/2 (0.025) and 0.05/1 (0.05) for the remaining two t-tests, respectively. Power for this study is defined as the probability that at least one of the three t-tests of the arm effect on VO_2_peak is significant; in other words, power is the probability that the first of the 3 ordered t-tests are significant. We assume that change in VO_2_peak will have a standard deviation of 4.0 mL ^.^ kg^-1 .^ min^-1^ as observed in previous research [27,36]. Statistical power depends upon the configuration of mean change in VO_2_peak across the 4 arms. Thus, for example, 80% power is obtained when the mean change in VO_2_peak across Arms 1, 2, 3, and 4 is 0.60, 0.60, 2.10, and 0.0 (mL ^.^ kg^-1 .^ min^-1^), respectively.

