#### ***Analytic plan***

The intention-to-treat analysis includes all randomized participants in their randomly assigned allocations. The intervention group assignment will not be altered based on the participant's adherence to the randomly allocated study arm. Patients who are lost-to-follow-up are included in the analysis (intention to treat). For the primary analysis, a multiple regression model will be used to assess a change in VO_2_peak on study group, the baseline value of the endpoint, and other pertinent baseline variables that may influence change in the study endpoints (e.g., co-morbid conditions/medications, self-reported exercise history, age). Data from PROs will be presented as mean, standard deviation (SD), median and inter-quartile range (IQR) and all change scores (value at follow-up minus value at baseline) will be presented with a 95% confidence interval.

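### Randomisation is stratified by VATS versus thoracotomy, but the Holm-controlled t-tests carry no stratum term: a small, conditional loss of precision that costs nothing to remove

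*Protocol article*

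**What the plan says.** Under Group allocation (Randomization), the protocol article says: "A permuted block design with allocation weight of 1:1:1:1 will be used to generate the treatment assignments". The same paragraph adds that "patient randomization will be stratified based on type of surgery, VATS versus thoracotomy surgery", and gives similarity of the groups at baseline as the reason. Type of surgery is the only stratification factor named.

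Under Sample size calculation, for each primary and secondary endpoint, "three separate t-tests will be used to compare each experimental arm to the control arm in mean change across time of the endpoint". Multiplicity over these three tests is handled separately within every outcome, where "the overall alpha level will be controlled at a two-sided 0.05 by using Holm's procedure". The definition of power refers to these same t-tests.

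Under Analytic plan, the primary analysis is described differently: "a multiple regression model will be used to assess a change in VO_2_peak on study group, the baseline value of the endpoint", together with other relevant baseline variables, illustrated by "e.g., co-morbid conditions/medications, self-reported exercise history, age". Type of surgery is not among the examples, but the list is open.

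The section on disease-related outcomes says that extent of surgery will be related to the intervention effect. It does not make type of surgery a term in an arm comparison.

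**The concern.** Stratified allocation balances the arms on type of surgery, so differences between VATS and thoracotomy patients largely drop out of the true sampling variance of an arm difference. A two-sample t-test does not know this. It estimates its error from the total spread within each arm, and that spread still contains the difference between surgery types. If type of surgery is prognostic, the reported standard error exceeds the true one, p-values are conservative and confidence intervals are too wide.

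The tests that carry the multiplicity control therefore do not analyse the trial as it was randomised, and part of what stratification could deliver is not collected. At stake is precision, not validity.

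**Working it through.** **Inputs from the article.** SD of change in VO2peak 4.0 mL/kg/min; 95 patients per arm; first Holm step 0.05/3 = 0.0167 two-sided; illustrative mean changes 0.60, 0.60, 2.10 and 0.0 in Arms 1 to 4 (all from Sample size calculation). VATS share above 60% at the operating hospital (Background); 60% is used, with 70% as a check.

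**Assumed, because the article gives no figure.** The difference d in mean VO2peak change between VATS and thoracotomy patients: 0, 1, 2 or 3 mL/kg/min, with the total SD held at 4.0.

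**The plan's own power figure.** The article states 80% power for that configuration. Simulating the probability that at least one of the three t-tests reaches p < 0.0167 gives about 88.6% to 88.7% with 95 per arm, so the figure does not reproduce as stated. About 76 evaluable patients per arm gives 79.5%, and 76/(1 − 0.20) = 95, so an unstated 20% loss would explain it. That mismatch is a separate matter. The comparison below uses 95 per arm on both sides.

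**Step 1: share of variance explained by the stratum.** R² = p(1 − p)d²/SD² = 0.6 × 0.4 × d²/16. For d = 1, 2, 3 this is 0.24/16 = 0.015, 0.96/16 = 0.06 and 2.16/16 = 0.135.

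**Step 2: standard errors.** The t-test reports SD × √(2/n) = 4 × √(2/95) = 0.580. Under stratified allocation the true value is 0.580 × √(1 − R²). The overstatement is 1/√(1 − R²) − 1.

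**Step 3: actual size of the unadjusted test.** The critical value at 0.0167 two-sided is 2.394, so the size is 2 × [1 − Φ(2.394/√(1 − R²))].

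**Step 4: power, like for like.** Both analyses are evaluated under stratified allocation, using the article's definition (at least one of three tests significant), by simulation.

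| d | R² | True SE | SE overstated by | Size at nominal 0.0167 | Power, unadjusted | Power, adjusted |
|---|---|---|---|---|---|---|
| 0 | 0 | 0.580 | 0% | 0.0167 | 88.7% | 88.8% |
| 1 | 0.015 | 0.576 | 0.8% | 0.0159 | 88.9% | 89.4% |
| 2 | 0.060 | 0.563 | 3.1% | 0.0135 | 89.4% | 90.9% |
| 3 | 0.135 | 0.540 | 7.5% | 0.0101 | 90.3% | 93.2% |

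The gain is about 0.5 points at d = 1, 1.5 at d = 2 and 2.9 at d = 3.

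**Hand check, Arm 3 against control only, d = 2.** 2.10/0.580 = 3.618. Unadjusted: Φ((3.618 − 2.394)/0.9695) = 0.897. Adjusted: Φ(3.618/0.9695 − 2.394) = 0.910. The gain is 1.3 points.

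**70% VATS.** Sizes become 0.0160, 0.0139 and 0.0108 for d = 1, 2, 3, so the effects are slightly smaller.

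**Direct simulation** of stratified blocks of four (8,000 trials). At d = 2 the arm difference had an empirical SD of 0.567 against a mean reported t-test SE of 0.580; the adjusted SE was 0.562. The simulated size at d = 2 was 0.0151, with Monte Carlo error √(0.0167 × 0.9833/8000) ≈ 0.0014, too coarse to separate 0.0135 from 0.0167. An extreme case, d = 4, makes the direction plain: SD 0.501 against 0.580, and size 0.0060 unadjusted against 0.0165 adjusted.

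**The case against.** The strongest case for leaving the text alone runs as follows. The Analytic plan names a regression as the primary analysis, and its covariate list is only illustrative. A stratum known at randomisation fits the description of a relevant baseline variable, and a journal article can leave the final list to the analysis plan. The t-tests appear under a sample size heading. The article gives balance at baseline, not prognostic value, as the reason for stratifying, and reports no effect of type of surgery on VO2peak change. The error is on the safe side.

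Much of this stands:

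- A reader might infer that the primary regression leaves the stratum out. The text does not support that: type of surgery is not named, but it is not excluded. The firm part of the point is the t-tests, which the article commits to for every endpoint and which carry the Holm procedure.
- A reader might infer that precision is certainly lost. It is lost only if type of surgery predicts the outcome; at d = 0 nothing is lost.
- The figures describe the t-tests with the unadjusted SD of 4.0. In a regression that already holds the baseline value and other covariates, the stratum's added contribution has not been computed, and would be smaller where it overlaps with them.
- The d = 3 case is 1.5 times the article's smallest relevant treatment difference of 2 and should be read as an upper illustration.

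What does not stand is that this is only a detail left for later. The article states which tests control the error rate, and those tests have no place for the one factor used to stratify.

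**Conclusion.** The point holds as a free improvement. The design is stratified by type of surgery, while the stated Holm-controlled tests are not. Under the assumptions above (60% VATS, total SD 4.0, 95 per arm), differences of 1 to 2 mL/kg/min between surgery types overstate the t-test standard error by about 1% to 3% and cost about 0.5 to 1.5 points of power. A difference of 3 would overstate it by about 7.5%.

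Two stronger readings should be resisted. A reader might infer that ignoring the stratum threatens validity. It does not: the estimates are not biased, and the type I error is at or below nominal. A reader might also set adjusted power against the power of a trial with no stratum effect, for example 90.9% against 88.7% at d = 2, and read a gain of 2.2 points. Stratified allocation already lifts the unadjusted test to 89.4%, so the gain attributable to adjusting is 1.5 points.

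Confidence is high on existence and direction. The size rests wholly on an assumed effect of type of surgery.

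**What to change.** Name the stratum as randomised as a fixed covariate in the primary regression and in the corresponding models for the secondary endpoints. Take the three arm-versus-control comparisons, and their Holm-adjusted p-values, from those models instead of from the unadjusted t-tests. Adding the term without moving the Holm comparisons would leave the stated tests unchanged.

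Define the covariate as the approach planned at randomisation. Allocation follows the baseline assessment, and Groups 1 and 2 exercise before surgery, so the stratum can only be the planned approach. The approach finally performed is a post-randomisation variable and should not replace it. The article does not propose that substitution, but its wording (type of surgery) leaves the definition open.

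The cost is one model term and a sentence or two of text. The data are already held for randomisation, and no change to sample size or conduct is needed.
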